## Abstract

**Background:**

Clinical evidence is commonly obtained through individual trials that are time-, cost- and resource-consuming, and which often leave unanswered clinically relevant questions. Umbrella studies have been developed to address the need for more efficient and flexible trial structures, predominantly for cancer treatments. The umbrella concept foresees data collection within a unifying trial structure, to which one or more substudies may be added at any time to address product- or therapy-specific questions. To our knowledge, the umbrella concept has not yet been used in the medical device area, but it may offer similar advantages as in other settings, particularly in areas where multiple therapies are available within one large treatment area.

**Methods:**

The MANTRA study (NCT05002543) is a prospective, global, post-marketing clinical follow-up study. The aim is to collect safety and device performance data covering the Corcym cardiac surgery portfolio for the treatment of aortic, mitral, and tricuspid valve diseases. The study uses a master protocol that outlines the main common parameters, and the specific questions are addressed in three substudies. The primary endpoints are device success at 30 days. Secondary endpoints include safety- and device performance-related data at 30 days, 1 year, and then annually through to 10 years. All endpoints are defined according to the more recent guidelines for heart valve procedures. Additionally, procedure and hospitalization information are collected, including Enhanced Recovery after Surgery in sites using such protocols, and patient outcome measures such as New York Heart Association classification and quality-of-life questionnaires.

**Results:**

The study started in June 2021. Enrollment in all three substudies is ongoing.

**Conclusions:**

The MANTRA study will provide contemporary information on the long-term outcomes of medical devices for the treatment of aortic, mitral, and tricuspid heart valve diseases in routine clinical practice. The umbrella approach adopted in the study has the potential of longitudinally assessing long-term efficacy of the devices and the flexibility to investigate new research questions as they arise.

## Background

Traditionally, clinical investigations in the medical device area have been conducted using individual study protocols designed for specific devices or device groups. The aim of such studies is to investigate safety and performance according to predefined endpoints and corresponding statistical analysis plans (SAPs). Any change to the study design and scope of the investigation mandated protocol amendments. Device improvements, iterations, or expansion of the clinical indications require new pre- or post-marketing studies, delaying product launch and requiring more resources from the manufacturers. In addition, regulatory requirements have evolved over time, and ad-hoc analyses are now frequently requested. Therefore, clinical scientists have been exploring novel study designs to increase flexibility without necessarily increasing time and costs of these studies. New ways to conduct clinical investigations, to collect data in one common platform, and to perform complex analyses have been explored in the pharmacological area for several years. In this context, adaptive investigational pathways have been adopted to address several questions simultaneously. Master protocols have been used in various contexts, outlined in Table 1 [1], whereby an overarching (“umbrella”) protocol exits under which multiple parallel studies are conducted. According to Park et al. [2], no umbrella trials have been conducted outside the field of oncology.

**Table 1 Tab1:** Master protocol trials and corresponding objectives, according to Woodcock and LaVange, 2017 [1]

Trial type	Objective
Umbrella	Multiple targeted therapies in the context of a single disease
Basket	A single targeted therapy in the context of multiple diseases or disease subtypes
Platform	Multiple targeted therapies in the context of a single disease in a perpetual manner, with therapies allowed to enter or leave the platform on the basis of a decision algorithm

Although umbrella studies have been conducted in pharma trials, to our knowledge this is the first such study to apply this concept in the medical device field.

Even though the concept of an umbrella protocol is new to the medical device area, the main advantages are equally as applicable, in particular for device manufacturers having several treatment options in their portfolio that can be used in similar treatment groups or interventional areas such as cardiac surgery. The CORCYM Mitral, Aortic aNd Tricuspid Post-maRket Study in a reAl-world Setting (MANTRA) (NCT05002543), sponsored by Corcym S.r.l., is the first clinical trial in the medical device area to adopt the umbrella protocol concept. MANTRA will use a single database to provide post-marketing clinical follow-up data of the entire cardiac surgery portfolio developed by the company for the treatment of heart valve diseases. The common denominator is heart valve disease and the same interventional area (heart valve cardiac surgery) within similar treatment groups, whereas product- and endpoint-focused questions related to the different indications will be addressed in the various substudies and by dedicated analyses of the data obtained through customized case report forms (CRFs).

## Methods

The MANTRA study protocol currently foresees three substudies, outlined in Fig. 1. These substudies target long-term post-marketing safety and device performance data in the treatment areas served by the Corcym product portfolio (manufactured by Corcym S.r.l., Italy, and Corcym Canada Inc.), including data on product accessories such as delivery systems and sizers. Study concept development and data collection have been extensively supported by a Steering Committee consisting of expert cardiac surgeons and cardiologist.

**Fig. 1 Fig1:**
[figure not shown]
Umbrella structure for the MANTRA study, encompassing heart valve disease

Depending on the Corcym devices used, different institutions can participate in one or more substudies. The study allows for inclusion of isolated as well as combined procedures with multiple device implantation (Sponsor or non-Sponsor devices), with the possibility to follow Corcym safety and performance information on all of the devices implanted and the possibility to collect data on interaction of multiple valve treatments.

The main objective of the aortic and mitral/tricuspid substudies is to monitor the ongoing safety and device performance of the commercially available Corcym products and accessories used for the treatment of aortic and mitral/tricuspid valve disease in a real-world setting, based on standard-of-care data collection. The third substudy focuses on the MEMO 4D device, an advanced technological evolution within the mitral portfolio. This substudy takes advantage of a dedicated echocardiographic CoreLab (Department of Medicine and Surgery, University Milano-Bicocca, Department of Cardiology, Istituto Auxologico Italiano, IRCCS, Milan, Italy) analysis of the product characteristics linked to specific hemodynamic parameters.

### Study design and population

MANTRA is a prospective, multi-arm, global, post-marketing study with long-term follow-up planned through to 10 years. Review and approval by a certified local ethical committee or institutional review board is needed for the master protocol and substudy protocol(s) as per local regulations. All subjects are required to provide informed consent before undergoing any clinical investigation-specific assessments (e.g. quality of life) and treatments.

The plan is to enroll approximately 2150 subjects in around 130 sites worldwide over 4 years, (1650 in the aortic substudy, 300 in the mitral/tricuspid and 200 in the MEMO 4D substudy) with follow-up visits scheduled at the time of hospital discharge, at 30 days after the procedure, and then annually up to 10 years (Figs. 2 and 3). Participants diagnosed with heart valve disease who are suitable to undergo valve replacement with a Corcym device per the approved instructions for use and who are willing to comply with the follow-up schedule can be included. Subjects participating in another clinical investigation that could confound the results of the MANTRA study and those with a life expectancy ≤ 12 months will be excluded. Subjects less than 18 years of age, pregnant or breastfeeding women, and other vulnerable populations (e.g. children, or subjects unable to sign informed consent or persons unlikely to be able to comply with follow-up) are not planned to be enrolled. In addition, long-term data obtained from participants treated with either the Perceval Plus™ device or treated with the Bicarbon™ prosthetic valve family and followed under a low international normalized ratio regimen from the SURE-AVR study (NCT02679404), will be transferred into the aortic substudy database.

**Fig. 2 Fig2:**
[figure not shown]
Study timelines study flow from screening to end of study

**Fig. 3 Fig3:**
[figure not shown]
Study flow from screening to end of study

### Endpoints

The primary endpoint is device success, adapted from the Valve Academic Research Consortium (VARC-3) [3] and from the Mitral Valve Academic Research Consortium (MVARC) guidelines [4] for the aortic substudy and for the mitral/tricuspid and MEMO 4D substudies, respectively. These two guidelines were developed by expert panels in an effort to provide guidance on the appropriate selection of clinical endpoints and definitions to increase consistency in the evaluation and reporting of trial outcomes. Secondary endpoints include mortality, morbidity, hemodynamics, procedural information (e.g. surgical times), intensive care unit management, and patient-related outcomes (e.g. New York Heart Association [NYHA] and quality-of-life improvement). Importantly, the definitions of complications, valve/ring degeneration for safety endpoints are aligned with the current VARC and MVARC guidelines to ensure homogenous reporting, adjudication, and comparison between devices and therapeutic strategies. Furthermore, the study will analyze patient related outcome endpoints, not only related to improvement of the NYHA class, but also considering the improvement of Quality of Life (Kansas City Cardiomyopathy Questionnaire, KCCQ-12) integrated with survival, as suggested by VARC-3 guidelines. Hemodynamic and structural performance from site-reported echocardiography findings, intra-operatively, discharge, at 30 days (+ 14 days), at 12 months after implant and at each subsequent follow-up collected as per the recommendations for the imaging assessment of prosthetic heart valves [5] will be analyzed according to the different device indications. The full list of study endpoints is detailed in Table 2.

**Table 2 Tab2:** Aortic, Mitral/tricuspid, and MEMO 4D substudy endpoints

	Aortic substudy (n = 1650)	Mitral/tricuspid substudy (n = 300)	MEMO 4D substudy (n = 200)
Primary endpoint	Device success at 30 days (+ 14 days) adapted from VARC-3 guidelines: Technical success Freedom from mortality Freedom from surgery or intervention related to the device or to a major vascular or access-related or cardiac structural complication Intended performance of the valve (mean gradient < 20 mmHg and less than moderate aortic regurgitation)	Device success at 30 days (+ 14 days), adapted from MVARC guidelines: Procedural mortality or stroke; AND Proper placement and positioning of the device; AND Freedom from unplanned surgical or interventional procedures related to the device or access procedure; AND Continued intended safety and performance of the device	Device success at 30 days (+ 14 days), adapted from MVARC guidelines: Procedural mortality or stroke; AND Proper placement and positioning of the device; AND Freedom from unplanned surgical or interventional procedures related to the device or access procedure; AND Continued intended safety and performance of the device
Secondary endpoints	Safety and performance assessments at 30 days, 12 months, and annually after implant Collection of procedural and hospitalization information Patient outcomes	Safety and performance assessments at 30 days, 12 months, and annually after implant Collection of procedural and hospitalization information Patient outcomes	Safety and performance assessments at 30 days, 12 months, and annually after implant Collection of procedural and hospitalization information Patient outcomes

### Schedule of assessments

The study schedule, including assessments and time points, is detailed in Table 3. The schedule follows common standard-of-care practices and may vary across sites. Participants will be asked to complete quality-of-life questionnaires (KCCQ-12 [6] for all the participants and the 5-level EQ-5D version (EQ-5D-5L) [7] for those implanted with the Perceval Plus™ device) at baseline, 30 days, and at 1-year follow-up. Hemodynamic and structural performance (primary and secondary endpoints) will be based on site-reported echocardiographic evaluations for participants enrolled in the aortic and mitral/tricuspid substudies. Echocardiographic examination is planned preoperatively, intraoperatively (pre- and post-implant), at 30 days (+ 14 days) after implantation, at 12 months, and at each subsequent follow-up, if available, as reflected in the standard-of-care at each site. Long-term follow-up will include on-site visits or phone calls.

**Table 3 Tab3:** Study assessment schedule

Item	Screening/Baseline	Procedure	Hospital discharge	30 Days (+ 14 Days)	12 months (± 30 days)	Annual visits (to 10 years)
Informed consent, eligibility criteria, demographics, medical history, and risk factors, clinical assessment	X					
Vital signs	X		X	X	X	X
Anticoagulant and/or antiplatelet medication	X		X	X	X	X
Blood tests^a^	X^,^		X	X	X	X
Procedural details of implantation and concomitant procedures		X				
Intensive Care Unit (ICU management			X			
Hospitalization data			X			
Pain score assessment (visual analogue scale)			X^b^	X^b^		
Echocardiography^c^	X	X	X	X	X	X
Computed tomography^d^	*X*	*X*	*X*	*X*	*X*	*X*
Electrocardiogram	X		X	X	X	X
NYHA class	X		X	X	X	X
QoL questionnaire^e^	X			X	X	
Serious adverse events		X	X	X	X	X
Device deficiencies		X	X	X	X	X
Accessories deficiencies		X				

^a^White blood cell, red blood cell, hemoglobin, hematocrit, platelets, serum lactate dehydrogenase, haptoglobin, reticulocyte, plasma free hemoglobin, serum creatinine (preoperatively and at discharge visit only), and international normalized ratio/quick. Plasma free hemoglobin will be collected only at sites that have the local capabilities of performing the evaluation. Blood tests baseline ideally be taken on admission, but in any case, not ≥ 7 days before the procedure

^b^Ideally pain score assessment should be collected and entered at post-operative on day 1, day 3, at discharge, and 30 days postoperative

^c^Including collection of images for analysis by Core Lab 3D TEE or 3D TTE images in accordance to standard of care

^d^Computed tomography is optional; only when done as standard of care

^e^KCCQ-12 questionnaire for all the subjects. EQ-5D-5L questionnaire also to be completed by participants implanted with Perceval Plus

For participants enrolled in the MEMO 4D substudy, the echocardiographic parameters reported from the independent echo core laboratory will be analyzed as primary and secondary endpoints. In addition, independent core laboratory evaluation using advanced imaging techniques (intraoperative 3D transesophageal echocardiography and 3D transthoracic echocardiography during follow-up) will be performed to analyze the relationship between the saddle-shaped MEMO 4D annuloplasty ring and the annular motion post-implant and throughout follow-up. Details are described in the echocardiographic protocol.

### Data management and monitoring

Study data will be collected using a web-based electronic data capture system (Merative Clinical Development [formerly IBM Clinical Development EDC system], Ann Arbor, Michigan, USA). Data will be continuously reviewed for omissions, errors, and values requiring further clarification using computerized and manual procedures. Serious adverse events, medical history, and concomitant medications will be coded using standard dictionaries.

Monitoring of the clinical investigation will be an interactive process overseen by the Sponsor monitoring team to ensure that high-quality data is obtained and that the study is conducted in compliance with the protocol, clinical study agreement, applicable laws, regulations, and good clinical practice as established in the Sponsor’s monitoring plan.

The study will be using a risk-based monitoring approach that will include both on-site and centralized monitoring (evaluation without visiting the study site) activities, including full (informed consent and serious adverse events) or partial source data verification, depending on data review findings. Activities of centralized monitoring may include statistical monitoring, contact with the site by telephone, web, or email, examining data quality with programmed data-monitoring checks, and review of adverse events. The intent is to ensure adequate protection of participants enrolled in the study and to ensure the quality and integrity of the study data while focusing resources on the most critical data elements and processes necessary to achieve the study objectives.

### Statistical analysis

Given the non-confirmative nature of the aortic and mitral/tricuspid substudies, neither formal sample size calculations nor formal hypothesis testing will be conducted. In contrast, a sample size calculation was performed for the MEMO 4D substudy, with the endpoint defined as restoration of annular height commissural width ratio (AHCWR) at end-diastole and end-systole at 12 months (± 30 days) after implantation compared with values measured at baseline (improvement versus baseline in AHCWR at post-implant time points indicates that the valve is functioning properly). The sample size calculation was performed only for saddle-shaped size MEMO 4D mitral annuloplasty rings, using the *t-*test for paired means (i.e. before and after device implant) and the following parameters: 90% power, 1-sided 5% significance level, standard deviation of 8 and mean of 5% (assuming a baseline AHCWR of 15% and a postoperative value of 20% at 12 months). AHCWR values range from 20 to 30% when a mitral valve functions properly and from 10 to 17% for diseased valve [8–12]. The sample size calculated using the above parameters was 41 for MEMO 4D featuring a saddle-shape configuration (34−42 mm). The total study sample was 200 and it is projected that at least 60 participants will be treated with MEMO 4D saddle-shape configurated rings, therefore meeting the sample size requirement for the hypothesis testing.

The number and percentage of subjects with device success at 30 days according to the VARC-3 [3] and the MVARC [4] guidelines, along with each individual component, will be presented. According to their statistical distribution, continuous variables will be presented either as means (± standard deviations), minimum and maximum values, or median with interquartile ranges. Categorical variables will be presented as numbers and percentages.

Survival analyses will be conducted to analyze time-to-event variables. Participants without events will be censored at their last known event-free time point. Survival curves will be constructed using Kaplan–Meier estimates; the number of subjects at risk, of censored subjects, of events, and the event-free survival rate and 95% confidence intervals of the survival rate for each time interval will be presented in a summary table.

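### A gain over baseline in AHCWR does not show a properly functioning valve: by the article's own ranges, the MEMO 4D paired test can be positive with the 12-month mean short of 20%

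*Protocol article*

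**What the plan says.** All of this is in the Statistical analysis section of the protocol article.

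- The MEMO 4D sample size rests on an "endpoint defined as restoration of annular height commissural width ratio (AHCWR) at end-diastole and end-systole at 12 months", "after implantation compared with values measured at baseline".
- A parenthesis then gives the meaning of a gain: "improvement versus baseline in AHCWR at post-implant time points indicates that the valve is functioning properly".
- The only test described is a t-"test for paired means (i.e. before and after device implant"), at "90% power, 1-sided 5% significance level", with a "standard deviation of 8 and mean of 5"%, "assuming a baseline AHCWR of 15% and a postoperative value of 20% at 12 months".
- The next sentence gives the reference ranges: "AHCWR values range from 20 to 30% when a mitral valve functions properly and from 10 to 17% for diseased valve".
- The calculated size is 41 saddle-shaped rings, and at least 60 participants are projected to receive one.

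Nothing in the article ties a conclusion about restoration to passing 17% or to reaching 20%.

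**The concern.** Restoration and proper function are statements about where the 12-month value lies. A paired before/after test addresses a different question, namely whether the mean has moved up from baseline. The article joins the two by saying that improvement indicates proper function, while its own ranges leave room for a valve to improve and remain in the diseased range, or in the gap between 17% and 20%.

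The article confines formal hypothesis testing to the MEMO 4D substudy and bases that test on AHCWR. The Discussion expects the study's data to go to regulatory bodies. If the stated inference is carried into the report, a small rise in annular height ratio and a full return to the 20 to 30% range would be described in the same words.

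**Working it through.** **Inputs from the article.** Baseline mean 15%, 12-month mean 20%, so a change of 5 points; SD 8; one-sided 5%; 90% power; calculated n = 41; projected n at least 60; proper function 20 to 30%; disease 10 to 17%.

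**Assumptions.** The null is no change (implied by the paired test, not written out). SD 8 is the SD of the paired difference (the article does not say). n counts complete baseline and 12-month pairs.

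**Step 1: the plan's own figure.** The normal approximation gives n = ((1.645 + 1.282) × 8 / 5)² = 21.9, so 22. The noncentral t gives 24. The stated 41 is therefore not reproduced from the stated inputs; an SD of the difference of about 10.7 would give it. That is a separate matter, but it bears on the SD and is used in Step 5.

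**Step 2: smallest significant mean gain.** Formula: t(0.95, n − 1) × SD / √n, added to the baseline of 15%.

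| Complete pairs | Gain | 12-month mean | Position |
|---|---|---|---|
| 41 | 1.684 × 8 / √41 = 2.10 | 17.1% | just above the diseased range, short of 20% |
| 45 | 1.680 × 8 / √45 = 2.004 | 17.004% | just above 17% |
| 46 | 1.679 × 8 / √46 = 1.981 | 16.98% | inside the diseased range |
| 60 | 1.671 × 8 / √60 = 1.73 | 16.7% | inside the diseased range |

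So a significant mean at or below 17% requires at least 46 complete pairs.

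**Step 3: probability of a positive test when the true mean is short of 20%.** Noncentral t with noncentrality (change / 8) × √n, for one cardiac phase.

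| True 12-month mean | n = 41 | n = 60 |
|---|---|---|
| 17% (change 2) | 47% | 61% |
| 18% (change 3) | 76% | 89% |

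**Step 4: two cardiac phases.** The endpoint names end-diastole and end-systole, and the article does not say whether both must be significant. If both must be, the Step 3 figures are upper limits. For illustration, if the two results were independent and each had a true mean of 17%, the joint probability would be 0.61² = 0.37 at n = 60 and 0.47² = 0.22 at n = 41. Positive correlation would move these towards the single-phase values.

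**Step 5: sensitivity to the SD.** With the SD of 10.7 that would explain n = 41, the smallest significant gain is 1.671 × 10.7 / √60 = 2.31 (mean 17.3%) at n = 60 and 1.684 × 10.7 / √41 = 2.81 (mean 17.8%) at n = 41. Neither lies in the diseased range, and both are short of 20%.

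**The case against.** The strongest reply is that the article names the paired t-test as the basis of the sample size and writes out no null value and no success rule. It says that master and substudy SAPs exist and refers to a separate echocardiographic protocol. A threshold for restoration could sit in any of these, and its absence from an article is no fault. This stands. A reader might infer that any significant gain will be declared restoration; the article does not state that rule. It does state that improvement indicates proper function, and no SAP provision would make that sentence agree with the ranges beside it.

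A second reply is that the diseased-range result is conditional. It needs 46 or more complete pairs at SD 8 and baseline 15%. The 60 is a projection of participants treated, and follow-up echocardiography depends on each site's standard of care. A 25% loss leaves 60 × 0.75 = 45 pairs, just too few. This also stands. The broader result, a significant mean short of 20%, does not depend on it.

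Third, the primary endpoint of the substudy is device success at 30 days, not AHCWR, and continuous variables will be summarised descriptively, so a low 12-month mean would be visible. That limits the harm, but it does not correct the stated inference.

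It is also tempting to say that the paired analysis leaves out participants who died or lost the ring before 12 months. The article gives no analysis set or missing-data rule for AHCWR, and such rules belong to the SAP, so that reading is not supported.

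**Conclusion.** The statement that improvement over baseline indicates a properly functioning valve is wrong as written, because it conflicts with the ranges given in the same paragraph. Under a no-change null, SD 8 and baseline 15%, the test can be positive with an observed mean of 16.7% at 60 complete pairs or 17.1% at 41. With a true mean at the top of the diseased range it would be positive in 61% or 47% of trials for one phase, and in fewer if both phases are required. With a larger SD the just-significant mean moves above 17% but stays below 20%.

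Two stronger readings do not hold. One is that a positive test at the calculated size could come with a mean in the diseased range: at 41 pairs and the stated inputs it could not. The other is that the paired test must be replaced by a confidence bound above 17%. Such a bound could itself be met by a mean between 17% and 20%, which the article does not call proper function, and its power depends on a 12-month SD that the article does not give. The fault lies in the conclusion drawn from the test, not in testing for a change.

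**What to change.** 1. Delete the inference that improvement over baseline shows a properly functioning valve.
2. Keep the paired test and word its conclusion as an increase from baseline in AHCWR.
3. Report the 12-month mean AHCWR and the percentage of participants at or above 20%, each with a 95% CI, separately for end-diastole and end-systole.
4. Base any statement about restoration on those estimates, read against the article's own 20 to 30% range.

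The cost is a more modest claim from the paired test and a little extra analysis, with changes of wording in the protocol and SAP and no new data. The percentage will not be precise: near 50% with 60 participants, the 95% CI is about ±1.96 × √(0.25 / 60) = ±13 percentage points.

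### The only formal sample size in the study, 41 saddle-shaped MEMO 4D rings, does not follow from the inputs it is attributed to, which give 24 pairs

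*Protocol article*

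**What the plan says.** In the Statistical analysis section of the Protocol article, the aortic and mitral/tricuspid substudies have no formal sample size and no hypothesis test. The MEMO 4D calculation is therefore the only formal one in the study.

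- Endpoint: "restoration of annular height commissural width ratio (AHCWR) at end-diastole and end-systole at 12 months (± 30 days) after implantation", compared with baseline.
- Test: a t-"test for paired means (i.e. before and after device implant").
- Parameters: "90% power, 1-sided 5% significance level, standard deviation of 8 and mean of 5"%.
- Basis of the mean: "assuming a baseline AHCWR of 15% and a postoperative value of 20% at 12 months".
- Result: "The sample size calculated using the above parameters was 41 for MEMO 4D featuring a saddle-shape configuration".
- Adequacy: the article projects that "at least 60 participants will be treated with MEMO 4D saddle-shape configurated rings, therefore meeting the sample size requirement" for the hypothesis test.

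In this section the article gives no correlation between baseline and 12 months, no attrition allowance and no adjustment for measuring at two cardiac phases.

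**The concern.** A paired t-test is sized from four quantities: the mean difference, the standard deviation of the differences, the significance level and the power. All four appear to be printed, and the article ties 41 to them alone, so the figure can be checked directly. A standardised effect of 5/8 = 0.625 is fairly large, and 41 looks too many for 90% power at a one-sided 5% level.

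At stake is whether a reader can trust the one powered analysis in the study. The article judges 60 projected participants adequate by comparison with 41. If 41 cannot be reproduced, the reader does not know what variability was assumed or what power the comparison has.

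**Working it through.** **Inputs**, all from the Statistical analysis section: mean paired change δ = 20 − 15 = 5 percentage points; SD = 8, read as the SD of the paired difference because that is the SD a paired t-test uses; α = 0.05, one-sided; power 0.90.

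**Attempt to reproduce 41**

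Normal approximation: n = [SD × (z₀.₉₅ + z₀.₉₀) / δ]² = [8 × (1.645 + 1.282) / 5]² = 21.9, so 22 pairs.

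Exact method: power = P(T > t₀.₉₅,ₙ₋₁), where T is noncentral t with n − 1 degrees of freedom and noncentrality √n × 5/8.

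| Pairs | Power |
|---|---|
| 23 | 89.6% |
| 24 | 90.7% |
| 41 | 98.9% |
| 60 | 99.9% |

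The requirement is 24. The stated 41 is 41/24 = 1.71 times as large, which rounding or choice of formula cannot explain.

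**Variants that keep δ = 5 and SD of the difference = 8**

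- Two-sided 5% (equivalently one-sided 2.5%), 90% power: 29.
- One-sided 5%, joint 90% power for end-diastole and end-systole, treated as independent: 29.
- Attrition alone, from 24 to 41: 1 − 24/41, about 41% loss. From 29: 1 − 29/41, about 29% loss.

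**Changes that do reach about 41**, each needing something the article does not state or contradicting something it does

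- SD of the difference of about 10.6 to 10.75 instead of 8.
- Mean change of about 3.7 instead of 5, with SD 8.
- 8 as the SD at each occasion, with baseline-to-12-month correlation ρ. Then SD of the difference = 8 × √[2(1 − ρ)]:

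| ρ | SD of difference | n for 90% power |
|---|---|---|
| 0 | 11.3 | 46 |
| 0.1 | 10.7 | 41 |
| 0.3 | 9.5 | 33 |
| 0.5 | 8.0 | 24 |

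- Two-sided 2.5% with joint 90% power for two independent phases: 41.
- Two-sided 5%, 80% power, variance of two uncorrelated measurements, normal approximation: 40.19, so 41.
- One-sided 5% with 99% power, or two-sided 1% with 90% power: 42 each.

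Several unrelated routes arrive at or near 41, so the number does not reveal which one was used.

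**Does the conclusion about 60 survive?** Power with 60 complete pairs:

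| Reading | Power at 60 |
|---|---|
| SD of difference 8, one-sided 5% | 99.9% |
| SD of difference 10.7, one-sided 5% | 97.3% |
| SD 8 per occasion, ρ = 0, one-sided 5% | 95.9% |
| SD 8 per occasion, ρ = 0, two-sided 5% | 92.0% |
| Two phases jointly, two-sided 2.5%, SD of difference 8 | 98.7% |

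All exceed 90%.

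**The case against.** The strongest reply is that nothing depends on the error. On the printed inputs 41 is conservative, 60 is more conservative still, and the comparison is a single analysis in a subset of one substudy. The declared primary endpoint in all three substudies is device success at 30 days, which is reported descriptively. This stands as an argument about seriousness.

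A second reply is that the article is a condensed account. It mentions a master SAP and substudy SAPs, which may hold a correlation, an attrition allowance or an adjustment for two phases. Their absence here is therefore no fault. That also stands, but it does not rescue the sentence, which attributes 41 to the printed parameters.

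Three stronger readings are tempting and are not supported:

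- *The n, the power or the SD must be the wrong item.* The list is not complete. A different significance level or effect, an attrition allowance, or an allowance for the two phases could also explain 41.
- *The margin for missing 12-month images is thin.* This needs 8 to be a per-occasion SD with correlation near zero, which the article nowhere says. Even then, a requirement of 41 out of 60 tolerates 19/60, about 32%, missing pairs, and 46 out of 60 tolerates 14/60, about 23%. No missing-image rate is given against which to call that thin.
- *The test is underpowered.* The power figures at 60 complete pairs show otherwise.

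**Conclusion.** The point holds as an error in a stated figure. The printed inputs require 24 pairs for 90% power, and 41 pairs would give about 99%. This rests on reading 8 as the SD of the paired difference, the natural reading for the named test. If 8 is instead a per-occasion SD, the sentence is still incomplete, because 41 then needs an unstated correlation of about 0.1.

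The document does not show which input is misprinted or missing, and only the sponsor can say. The claim that 60 participants suffice survives under every reading examined, assuming complete pairs and a non-negative correlation. The article should be corrected, but neither the size of the substudy nor the primary endpoint is affected.

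**What to change.** Restate the calculation so that n, power and inputs agree, and say what the 8 refers to.

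- If 8 is the SD of the paired difference: give 24 pairs for 90% power, or keep 41 and state about 99% power.
- If it is not: give the SD of the difference, or the per-occasion SD with the correlation, that leads to 41.
- If 41 includes anything else, such as an attrition allowance, another significance level or effect, or an adjustment for end-diastole and end-systole, state it beside the figure.

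Make the same correction wherever the calculation is repeated, for example in the MEMO 4D substudy protocol or SAP. The cost is wording only, with no change in enrolment.
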